While evaluating the efficiency of the masking mechanism [17], which is routine in studies for the treatment of stroke and other diseases related to neuromodulation, biases may occur due to inadequate blinding of several people involved in the clinical trial, or by error allocation, the effect of the treatment, or co-interventions [76]. Unlike blindness, these bias-generating consequences can be measured [77]. To this end, the example of another study using external judges [78] will be applied in this work, a final evaluation involving neurologist doctors accompanying the patients in their clinical treatment. These professionals will not be aware of behavior and interventions applied in this experiment. The imaging tests carried out for the diagnosis of vascular injury will be repeated and evaluated by these doctors at the end of intervention (T1) as a routine consultation procedure. After analysis of these imaging tests, the doctors will be asked whether they believe that the patient has suffered some consequential event which can act as an external assessment tool for a clinical trial. Reports of biased results can be examined as to whether the degree of agreement between the opinion of an external judge (neurologist) and the trialists (involved in outcome assessments and physical therapy interventions with CIMT) will be the same for both experimental and control participants.

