Regarding safety, deleterious adverse and cognitive effects will be recorded/computed in terms of the proportion in each group, in each time period (T0, T1, and T2), and will be analyzed by the Fisher exact test.

Bias-generating will be tested. The statistical model used for blinding effectiveness was based on the study of Brunoni et al. [97]. The chi-square test or Fisher’s exact test will be used to assess if tDCS blinding guessing was beyond chance for patients, external judges, and trialists. Paired *t*-tests will be used to compare the rate of their guessing according to the Likert scale. Logistic regressions exploring the factors associated with “correct blinding guessing” (that is, participants who correctly guessed their allocation group) will be performed. The factors will be clinical response, high guessing confidence (scores 4 or 5 on the Likert scale), and adverse effects.

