### Sample size

The sample size was estimated based on previous studies using matched groups of non-invasive stimulation with rehabilitation [98, 99]. The power calculations to determine the number of participants in each group were determined in relation to the expected change in BI because it is commonly used in tDCS studies of patients after stroke [30, 31].

According to Khedr et al. [30], the mean expected improvement is about 10 points, with a standard deviation (SD) equivalent to 7 points. Thus, a calculation considering 90 % power suggests that it would take at least 12 patients in each group to detect the difference found corresponding to the effect of active or placebo tDCS.

Considering the possibility of sample loss during the study (withdrawal, inability to continue the treatment, mortality), 20 patients will be included per group, totaling 40 participants (SPSS Ver.20.0; SPSS Inc., Chicago, IL, USA). The analysis will be performed at a 0.05 significance level.

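### The bias check asks whether judge–trialist agreement is the same in both arms, but none of the named tests compares that agreement between arms

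*Protocol article*

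**What the plan says.** Randomization and blinding in the protocol article brings in neurologists as external judges. After reviewing repeat imaging at the end of the intervention (T1), they are asked "whether they believe that the patient has suffered some consequential event". The section then gives the criterion for bias: whether "the degree of agreement between the opinion of an external judge (neurologist) and the trialists", the latter being those who assess outcomes or deliver CIMT, "will be the same for both experimental and control participants".

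Data analyses takes this up with the sentence "Bias-generating will be tested" and lists three analyses:

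- chi-square or Fisher tests to "assess if tDCS blinding guessing was beyond chance for patients, external judges, and trialists";
- paired t-tests, which "will be used to compare the rate of their guessing according to the Likert scale";
- logistic regressions on correct guessing, with clinical response, high guessing confidence (Likert 4 or 5) and adverse effects as factors.

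The section does not say which ratings form a pair or how arm enters the paired tests.

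**The concern.** The stated question is a between-arm contrast of a quantity formed within each patient from two raters. A paired t-test has a different null hypothesis, that two mean ratings are equal. Two raters can have equal means and still disagree on many patients. They can also differ by a constant on every patient in both arms, which is a difference in how they use the scale and not differential bias. The other two analyses concern guessing against chance and predictors of a correct guess.

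If the plan is followed as written, its own bias question goes unanswered. A significant paired test could then be reported as evidence of bias when it shows only a general difference in level between raters. Such a difference is plausible here: CIMT staff supervise three hours of training daily, while the neurologist gives an opinion at a routine consultation.

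**Working it through.** **Question against tests.** The criterion needs (i) a judge–trialist pair for each patient, (ii) a measure of agreement and (iii) a comparison of arms.

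- Chi-square/Fisher on guessing: each rater type against chance; no judge–trialist pair.
- Paired t-test: can use the pair, but compares means and has no between-arm contrast.
- Logistic regression: neither arm nor rater agreement is among the listed factors.

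None supplies all three.

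**Inputs.** From Sample size: 20 per group, and "The analysis will be performed at a 0.05 significance level" (two-sided assumed). The document gives no figure for the bias check. Its only sample-size result is for the Barthel index: "a calculation considering 90 % power suggests that it would take at least 12 patients in each group". That figure reproduces: with a difference of 10, SD 7 and 90% power, the t-based calculation gives 11.35, so 12 per group. Twelve per arm serves below as a low case.

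**Model.** Let D be the trialist-minus-judge Likert difference for a patient, with an assumed SD of 1. The assumed mean of D is dA in the active arm and dS in the sham arm. No differential bias means dA = dS.

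- Paired test over all patients: t = mean(D) / (s/√40)
- Paired test within one arm: t = mean(D) / (s/√20)
- Between-arm test: t = [mean(D, active) − mean(D, sham)] / [s√(2/20)]

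Rejection rates from 10,000 simulated trials per scenario, 20 per arm, normal D:

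| dA / dS | Paired, all patients | Paired, active arm only | Between arms |
|---|---|---|---|
| 0 / 0 | 4.7% | 4.9% | 5.1% |
| +0.5 / +0.5 | 86.8% | 56.8% | 5.2% |
| +0.5 / −0.5 | 2.9% | 56.7% | 86.4% |
| +1 / −1 | 0.6% | 98.9% | 100% |
| +1 / 0 | 81.2% | 99.0% | 86.7% |
| +0.5 / 0 | 31.9% | 56.4% | 34.0% |

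A check on the second row: the non-centrality of the all-patient test is 0.5 × √40 = 3.16, and within one arm it is 0.5 × √20 = 2.24. For +0.5/−0.5 the between-arm non-centrality is 1/√(2/20) = 3.16, while the pooled mean is 0.

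**Sensitivity to the assumptions.**

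- Rounded 1–5 scores: 81.2% for the common shift (all patients); for opposite shifts, 3.2% pooled against 80.7% between arms.
- 12 per arm: 65.3% for the common shift (all patients).
- SD 1.5 with shifts of 0.5 point (5,000 runs): 54% for the common shift; for opposite shifts, 4% pooled against 53% between arms.

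**The case against.** The strongest reply is that the paired t-tests were never meant to carry the agreement question. The text around them concerns blinding effectiveness, and the Likert score looks like confidence in an allocation guess. The neurologist's opinion is about a consequential event. On that reading the two sections describe different quantities, and the agreement comparison, worded only as something that can be examined, is simply left to a fuller document. This stands in part: the link between the sections is unclear. But the article announces the bias test, brings in the same judges and trialists, and lists the analyses. On either reading, the comparison it set up has no matching test among them.

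A reader might go further and infer three things that the document does not support:

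- **That the arms are pooled.** Data analyses does not say so. Paired tests run arm by arm would each detect a 0.5 SD shift about 57% of the time and a 1 SD shift about 99% of the time. Two separate p-values would still not be a test of the difference between arms.
- **That the check misses bias differing by arm in general.** It does so only when arms are pooled and shifts cancel. With bias in one arm, the pooled test is nearly as powerful as the between-arm test (81.2% against 86.7%; 31.9% against 34.0%), though it cannot say which arm is responsible. The chi-square/Fisher tests are also not blind to trialists whose guesses follow the true allocation.
- **That the paired test rejects falsely as a rule.** That needs a rater shift common to both arms. Without one it keeps its level (4.7%).

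**Conclusion.** The point holds in a limited form: the article states a between-arm question about judge–trialist agreement and names no analysis that answers it. This rests on the text alone and needs no assumption. The paired t-tests cannot fill the gap, because they test equality of mean ratings.

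The size of the possible error is conditional. False signals of about 87% (all patients) or 57% (one arm) require a common shift of 0.5 SD. The loss from 86% to 3% requires both pooling and cancelling shifts. The SDs and shifts are assumptions, since the document gives none for the Likert ratings. The matter is confined to an ancillary check and does not touch the analysis of the Barthel index or the secondary outcomes. It should be corrected, because the trial's credibility rests partly on its blinding.

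**What to change.** In Data analyses:

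1. State which judge opinion and which trialist opinion are paired for each patient, and reconcile the consequential-event opinion under Randomization and blinding with the allocation guess in Data analyses.
2. Add the between-arm comparison. For categorical opinions, report the proportion of agreement (or weighted kappa, if ordinal) by arm, and its difference with a 95% CI. For Likert ratings, compare the trialist-minus-judge difference between arms (the rater-by-arm interaction) with a 95% CI. The second does not replace the first, since equal mean differences do not imply equal agreement.
3. State that the paired t-tests describe differences in level between raters and are not the test of differential bias.

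The cost is wording only; the opinions are already planned. Precision will be low. At 20 per arm and 50% agreement in each arm (the least favourable case), the 95% CI half-width for the difference in agreement is 1.96 × √(2 × 0.25/20) = 0.31. The result should therefore be reported as an estimate with its interval, and a non-significant result should not be read as absence of bias.

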### Outcomes

For analysis of the primary endpoint, the Barthel index (BI) was chosen because it is commonly used in studies related to post-stroke rehabilitation, adequately reflecting clinical practice [47–49]. This instrument is designed to assess the patient’s level of independence to perform ten basic life activities: eating, bathing, personal care, ability to dress themselves, motility, urinary regularity, bathroom use, chair-bed transfer and vice versa, mobility, and climbing stairs [50]. The literature on the minimal clinically important difference detected by the BI shows that a change of 2 points is meaningful and beyond measurement error. This calculation refers to a modified BI with scores of 0–20 points [51]. Since the changes in the values of the scores do not affect other properties of the scale, it is considered equivalent to the original version, with scores of 0–100 points [52]. Thus, taking the original scale used in this study as a reference, clinical improvement will be considered as a final score higher than 10 points (T2) according to the BI, compared to baseline (T0) before the therapeutic protocol [30].

The BI has been reported with excellent levels of reliability, validity, and adequate responsiveness to change in several countries [52, 53]. In a study of 121 patients at four post-stroke period points (14, 30, 90, and 180 days), the inter-rater reliability using a weighted kappa varied from 0.53 (adequate) to 0.94 (excellent). The inter-rater reliability for the total score, calculated using the intraclass correlation, was 0.94 (excellent). The internal consistency, calculated using Cronbach’s alpha, was excellent, varying between 0.89–0.92 [54]. The construct validity was also confirmed by Wilkinson et al. [55], with rank correlation coefficients of the BI with the SF-36 (Medical Outcomes Study 36-item Short-Form Health Survey) subscales being found in patients with their first-ever stroke varying from r = 0.22 (Role Emotional subscale) to 0.81 (Physical Functioning Profile subscale).

Secondary outcome measures include the Modified Ashworth Scale, the 30-item Motor Activity Log, the Biodex Balance electronic platform, the Postural Assessment Scale for Stroke, the Falls Efficacy Scale, the Medical Research Council scale, the Short Physical Performance Battery, the Wolf Motor Function Test, and the SF-36.

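### The blinding regression models correct guessing with no term for arm, so its coefficients for clinical response and adverse effects cannot show whether these drive the guesses

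*Protocol article*

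**What the plan says.** The last paragraph of Data analyses in the protocol article sets out the blinding assessment in separate steps.

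- A chi-square or Fisher's exact test is planned "to assess if tDCS blinding guessing was beyond chance for patients, external judges, and trialists".
- Logistic regressions then take correct guessing as the outcome, with the predictors listed directly after it: "participants who correctly guessed their allocation group) will be performed. The factors will be clinical response, high guessing confidence" (a Likert score of 4 or 5) and adverse effects. Neither allocated arm, nor an interaction with arm, nor a separate fit in each arm is mentioned.

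Two other sections bear on the point.

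- Outcomes defines response on the Barthel index (BI): "clinical improvement will be considered as a final score higher than 10 points (T2) according to the BI, compared to baseline (T0").
- Randomization and blinding describes the external judges, who are neurologists reviewing repeat imaging at T1. The question it gives for them is that "the doctors will be asked whether they believe that the patient has suffered some consequential event".

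**The concern.** The regression is meant to explain correct guesses: did patients work out their arm because they improved, or because of what they felt? Both prompts push the guess towards active, whichever arm the patient is in. Under sham, a patient who improves and so guesses active is wrong. A model of correctness without arm averages a positive effect in one arm with a negative effect in the other.

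A coefficient near zero could then be reported as evidence that neither response nor sensations influenced the guesses when they did. A negative coefficient could be read as response making patients worse at guessing. The argument covers response and adverse effects. It does not cover guessing confidence, which has no built-in direction towards active.

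A lesser matter concerns the judges. Their guessing is to be tested against chance, but the question described for them is about a clinical event, and an answer to it cannot be scored as a right or wrong guess of allocation.

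**Working it through.** **Inputs from the article.** Allocation is 1:1 with 20 per arm. Response is read as a BI gain of more than 10 points from T0 to T2. Sample size states that "the mean expected improvement is about 10 points, with a standard deviation (SD) equivalent to 7 points"; the 10 points are read as the difference between arms. That section's figure reproduces: 2 × (1.960 + 1.282)² × 7² / 10² = 10.3, so 11 per arm by the normal formula, and 11.35, so 12 per arm, by the two-sided t-test. The sample size is not at issue.

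**Assumed inputs.** a = P(guess active | responder) and b = P(guess active | non-responder), the same in both arms; rA and rS are the response rates under active and sham. The article gives none of these.

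**Within an arm.** The odds ratio (OR) for guessing active is [a/(1−a)] / [b/(1−b)]. With a = 0.8 and b = 0.3 it is 4 / 0.4286 = 9.3. For a correct guess it is 9.3 in the active arm and 1/9.3 = 0.11 under sham.

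**Without an arm term (equal arms).**

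- P(correct | responder) = [rA·a + rS·(1−a)] / (rA + rS)
- P(correct | non-responder) = [(1−rA)·b + (1−rS)·(1−b)] / (2 − rA − rS)

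*Illustrative response rates, a = 0.8, b = 0.3*

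| rA / rS | P(correct), responder | P(correct), non-responder | OR |
|---|---|---|---|
| 0.50 / 0.50 | 0.50 | 0.50 | 1.00 |
| 0.60 / 0.40 | 0.56 | 0.54 | 1.08 |
| 0.70 / 0.30 | 0.62 | 0.58 | 1.18 |

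*Response rates from the trial's own difference.* With normally distributed gains, SD 7 and sham mean gain c, rA = Φ(c/7) and rS = Φ((c−10)/7).

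| Assumed c | rA / rS | P(correct), responder | P(correct), non-responder | OR |
|---|---|---|---|---|
| 0 | 0.50 / 0.08 | 0.72 | 0.56 | 2.03 |
| 5 | 0.76 / 0.24 | 0.66 | 0.60 | 1.25 |
| 10 | 0.92 / 0.50 | 0.59 | 0.65 | 0.78 |

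**Other guessing patterns, same three values of c.**

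- a = 0.8, b = 0.2 (within-arm OR 16): 1.79, 1.00 and 0.56.
- a = 0.9, b = 0.5 (within-arm OR 9): 3.85, 2.45 and 1.62.

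Cancellation is exact when rA = rS, or when rA + rS = 1 and a + b = 1. Elsewhere the coefficient is distorted.

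**Detection with 40 patients** (simulated trials, likelihood-ratio test at 0.05, response as the only factor besides arm).

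- a = 0.8, b = 0.3, illustrative rates: the planned model finds the response effect in about 2 to 4% of trials. A model of guessing active on arm and response finds it in about 86 to 92%.
- Same a and b, trial-based rates for c = 0, 5, 10: about 15%, 5% and 5%, against 75 to 81%.
- a = 0.9, b = 0.5, trial-based rates: about 11 to 44% for the planned model.
- Adding arm only as a main effect does not repair the model: at response rates of 70/30 detection is about 6%.

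Adverse effects follow the same algebra, with adverse-effect rates in place of response rates. No figure is given because the article supplies no expected rates.

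**The case against.** **Pooling is inferred.** The article never says the arms are pooled, speaks of regressions in the plural, and bases the blinding analysis on a cited study that is not at hand. A full analysis plan might fit each arm separately. This is fair, but the list of factors is worded as complete, and a model without arm is its natural reading.

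**Unblinding is tested elsewhere.** A reader might infer that the plan would show no unblinding at all, or that the response coefficient is always near 1. The documents support neither. The chi-square or Fisher test addresses guessing against chance, and the coefficient can be well away from 1, as the 0.9/0.5 pattern shows. Where response rates are equal, guesses that follow response carry no information about allocation, so a null result for correctness is the right answer to that question. What remains is that the chance test does not say why guesses were correct, which is the regression's job. That test is also weak at this size: with a = 0.8 and b = 0.2 it is significant in about 20% of trials at response rates of 70/30 and 36% at 76/24.

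**Adverse effects may differ by arm.** The sham current stops after 30 seconds, so sensations may be commoner under active current, and cancellation would then be incomplete. That is correct; the coefficient would still mix two opposite effects.

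**The judges.** A reader might infer that there will be no valid guess data from them. That is not shown. The article prints no allocation question for patients or trialists either, so its absence for judges may be condensation. What stands is a mismatch between the two sections.

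**Conclusion.** The point holds as a flaw in a secondary, exploratory analysis. If improvement or sensations prompt an active guess, correct guessing modelled without arm yields coefficients that may be attenuated, null or reversed, and these cannot show whether guesses follow response or adverse effects. Across the trial-based scenarios worked here, the planned OR for response ran from about 0.56 to 3.85 where the within-arm OR was 9 to 16. How far it is distorted depends on assumed guessing probabilities, taken as equal in both arms, and on an assumed sham gain; the reversal of direction between arms needs only that the prompt pushes guesses towards active in each arm. The judges' question and the test applied to it need reconciling, which is a lesser matter. The primary BI comparison and the sample size do not depend on any of this.

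**What to change.** In Data analyses, make the outcome of the regression whether the participant guessed active (yes/no), with arm, clinical response and adverse effects as factors. Alternatively, keep correct guess as the outcome, include arm and its interaction with each of these factors, and report the estimates by arm. A main effect of arm alone is not enough. Guessing confidence can stay as a predictor of correctness. The cost is a change of wording; the patient data are the same.

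For the external judges, either state in Randomization and blinding that they also give an allocation guess, or remove them from the chance test and keep their event assessment for the agreement comparison described there. The first costs one question at a consultation already planned. Trial status reports 40 participants randomized by the end of December 2015, so where those consultations have passed without a guess being recorded, removal is the practical option and costs nothing.

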## Methods

### Overview

This is a placebo-controlled, double-blind, randomized clinical trial (Fig. 1), in which 40 patients are divided into two groups of 20 participants each. In Fig. 1, the CONSORT (Consolidated Standards of Reporting Trial) flowchart [32] shows the number and distribution of participants: Group A1 - participants in post-stroke subacute stage that receive active tDCS combined with CIMT; Group A2 - participants in the post-stroke subacute stage who receive a placebo stimulation associated with CIMT. Patients will undergo three assessments: baseline (T0), week 2 (T1), and week 4 (T2). Neuropsychological tests will be performed at T0 and T2. Adverse events will be measured in each session, where the researcher responsible for administering the neurostimulation will question the patient on whether they experience any uncomfortable or painful sensation, and if this is related to the tDCS, following the procedure of Brunoni et al. [33]. At the end of the study, participants who received tDCS and showed clinical improvement will be invited to receive bimonthly stimulation for 12 months as part of a longitudinal study of tDCS for stroke. Those who received the tDCS placebo and did not respond will be invited to receive daily sessions with an active current for 10 days. Finally, those who had a response to the placebo will be referred for other physical therapy treatment.

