### Safety

With regards to adverse effects, patients will be asked at every stimulation session about the effects experienced such as “tingling,” “burning,” “headache,” “sleepiness,” and others, which they will then score in intensity (1 - no, 2 - mild, 3 - moderate, 4- strong), and this effect is related to the stimulation in a Likert scale of 1 (no relation) to 5 (strongly related) [33].

Regarding safety, deleterious cognitive effects, that is any effect from therapy detrimental to cognitive functions, will be analyzed using the following neuropsychological tests referenced in the literature: Montreal Cognitive Assessment (MoCA), which assesses cognitive dysfunction [87]; the Victoria version of the Stroop Color and Word Test, to measure executive functions [88]; the Digit Span subtest, which evaluates attention and (direct order) and working memory (indirect order) [89]. A cognitive evaluation will be conducted at the beginning and end of the study to check if there really are deleterious effects of neurostimulation, so that the values at baseline can be used as a reference.

We could find no literature reports of any deleterious cognitive effect after application of tDCS. It is considered a safe technique that has been used for several years in post-stroke patient treatment [9, 22, 33, 81].

If the patient experiences any loss or strong discomfort, the treatment will be stopped and medical care as well as physical and psychological therapy will be offered for control of potential problems and to promote recovery.

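### The logistic regressions of correct guessing put three factors to at most 40 patients without fixing how adverse effects are coded; ordinary fits are modestly inflated and may often fail if nearly every patient reports an effect

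*Protocol article*

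**What the plan says.** The Data analyses section announces "Logistic regressions exploring the factors associated with" correct blinding guesses, which it explains as "participants who correctly guessed their allocation group". It then lists the explanatory variables: "The factors will be clinical response, high guessing confidence (scores 4 or 5 on the Likert scale), and adverse effects". Only confidence is given a cut-point there. The section does not name an estimator, and it does not say whether the factors enter together or one at a time. It names SPSS 20, and R for multiple imputation.

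The other relevant statements are these:

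- Sample (Overview): "40 patients are divided into two groups of 20 participants each".
- Response (Outcomes): "clinical improvement will be considered as a final score higher than 10 points (T2) according to the BI", judged against baseline. This is a yes/no quantity.
- Adverse-effect collection (Safety): "patients will be asked at every stimulation session about the effects experienced such as" tingling, burning, headache, sleepiness and others. Patients "score in intensity (1 - no, 2 - mild, 3 - moderate, 4- strong", and they also rate relatedness to stimulation from 1 to 5.
- Sessions and sham (tDCS): ten sessions, with slight tingling and itching expected under sham as well.
- Safety analysis (Data analyses): adverse and cognitive effects "will be recorded/computed in terms of the proportion in each group" and compared by Fisher's exact test.

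**The concern.** Three explanatory variables are a lot for 40 patients. Ordinary logistic regression on so few outcomes pushes non-null estimates away from zero. It has no finite solution when a factor separates correct from incorrect guesses, or when a factor takes the same value in everyone.

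The adverse-effect factor is the one most exposed. Two of the three factors are naturally yes/no, and the only stated analysis of adverse effects elsewhere is a comparison of proportions, so an analyst could easily code this factor as any effect ever. With ten prompted sessions, and a sham that produces one of the prompted sensations, that coding could leave very few patients without an effect. This is the plan's only stated analysis of what drives correct guessing, and an adverse-effect estimate that is missing or unstable would leave that question unanswered.

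**Working it through.** **Plan's own figure.** The article gives no figure for this regression. The 40 comes from the Sample size section: a 10-point difference, SD 7, 90% power, 0.05 level. A two-sided two-sample t calculation gives 89.0% power at 11 per group and 91.7% at 12. The stated 12 is therefore reproduced, and it was raised to 20 per group for losses.

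**Rarer outcomes per factor.** Formula: 40 × (1 − proportion correct) / 3. The proportion correct is assumed, since the article gives none.

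- 50% correct: 20 / 3 = 6.7
- 65% correct: 14 / 3 = 4.7
- 75% correct: 10 / 3 = 3.3

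**How common any effect ever could be.** With independent sessions, the share of patients with at least one effect is 1 − (1 − p)^10, where p is the per-session rate. No p is given, so a range is shown, together with results that allow correlation between a patient's sessions (beta-binomial; the correlations are also assumed).

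| Per-session rate | Independent | Correlation 0.3 | Correlation 0.5 |
|---|---|---|---|
| 10% | 65% | 36% | 26% |
| 20% | 89% | 60% | 46% |
| 30% | 97% | 76% | 62% |

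Under independence, 90% is reached at p = 1 − 0.1^(1/10) = 0.206. With correlated sessions it takes a much higher rate.

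**How often an ordinary fit fails.** The simulation used n = 40, three independent binary factors (response 40%, high confidence 30%, adverse effects varied), a common odds ratio of 1, 2 or 3, about half of guesses correct, and 1,000 trials per setting. Failure means a constant factor or separation. The last column is an exact binomial calculation for the adverse-effect factor alone, with 50 and 65% correct.

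| Patients with any effect | Three factors together | Adverse effects alone |
|---|---|---|
| 30–70% | 0–4% | 0–1% |
| 80% | 4–10% | 3–6% |
| 90% | 26–37% | 24–29% |
| 95% | 61–68% | 60–63% |

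A simulation with other inputs (response 50%, high confidence 40%, 50 to 75% correct) gave 19 to 36% failures at 89% prevalence. If only 24 patients remained, the number the plan itself requires, the single-factor failure rate at 90% prevalence would be 0.080 + 0.424 = 50% (50% correct) to 0.080 + 0.465 = 55% (65% correct).

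**Bias where a fit exists.** At 30 to 70% prevalence, over the three factors:

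- True log odds ratio 0.693: maximum likelihood averages 0.75 to 0.83, Firth 0.67 to 0.75.
- True 1.099: maximum likelihood averages 1.21 to 1.29, Firth 1.07 to 1.16.
- True 0: no inflation.

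The extremes are 0.75 / 0.693 = 1.08 and 0.83 / 0.693 = 1.20, with most settings at 10 to 15%. The standard deviation of a single estimate is about 0.75 to 0.95, so an excess of 0.06 to 0.19 is minor beside the noise.

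**Very high prevalence.** For a true 0.693, the adverse-effect estimates that survive average 0.51 at 90% and 0.25 at 95%, which is attenuation. Firth gives 0.64 and 0.43 there, and gives nothing when the factor is constant.

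**The case against.** The strongest reply is that the article does not commit to the fragile specification. It names no estimator. The plural wording fits one-factor models as well as a joint one. The proportions sentence belongs to the safety comparison and does not define the blinding factor, and the graded ratings would support a score or a severity threshold. Coding and estimator are details that an article may leave to the full analysis plan. The analysis is already described as exploring, follows the chi-square or Fisher tests that assess blinding, and touches no primary or safety conclusion. A separated odds ratio would be obvious in the output.

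Most of this stands. A reader might infer that adverse effects will be entered as yes/no, that they will be near-universal, and that the estimates will in general be inflated or not exist. The documents do not support that. The coding is unstated, no rate appears anywhere, and below about 80% prevalence a finite estimate exists in roughly 90% or more of simulated trials. At very high prevalence the surviving adverse-effect estimate is too small, not too large.

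What remains is narrower. The article does fix the model type, the three factors and the sample. Logistic regression without qualification, with SPSS 20 named, ordinarily means maximum likelihood. Fitting adverse effects alone does not avoid the failure at 90% prevalence. The article allows an exact test for guessing against chance but offers no small-sample counterpart for the regression.

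**Conclusion.** The point holds as a minor, partly conditional improvement. If the factors are fitted jointly, there are about 5 to 7 rarer outcomes per factor at 50 to 65% correct guesses, and ordinary maximum likelihood overstates non-null log odds ratios by about 10 to 15%. That is modest beside the imprecision, and interval coverage is near nominal where fits exist.

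The more serious failure, no finite estimate in roughly a quarter of trials or more, needs two things the article does not state: an any-effect-ever coding, and about 90% or more of patients reporting an effect. The sham sensation and repeated prompting make this possible, but correlated sessions make it less likely than the independent-session figures suggest. The simulated rates also rest on assumed response and confidence rates and on independent factors.

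**What to change.** In Data analyses, state that the regressions of correct guessing use Firth's penalised likelihood with profile-likelihood intervals. State also that adverse effects enter as a graded per-patient score built from the intensity or relatedness ratings already collected, for example mean intensity over the ten sessions. The grading is the more important half, because penalisation cannot help a factor that does not vary and shrinks heavily when the factor is almost constant.

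The cost is a sentence or two of wording and one R routine outside SPSS (R is already named for imputation). No new data are needed. The downside is slight shrinkage of the estimates. Up to about 80% prevalence that shrinkage removes most of the bias and lowers root mean squared error by roughly 10%.
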